#### Ultrasound scan

For the ultrasound measurements (Sonido Smart Plus, Zimmer MedizinSysteme), the medial aspect of a linear 3.8-cm-long transducer will be placed longitudinally 2 cm lateral to the lumbar spinous processes, midway between lumbar vertebrae (L) 2 and L3 (Fig. 3). Measurements will be taken using a cine-loop technique with a single ultrasound beam focused on the thoracolumbar fascia with a 3.2 cm depth. During the measurement, the therapy table will pivot into the 45° position at a speed of 3°/s. The thickness of the single tissue layers in the starting and end position, as well as the shear motion between these positions, will be measured in millimetres (mm) [19, 20, 24]. The compressibility of the lumbar structures will be measured in the starting position using a force gauge attached to the transducer. An ultrasound image will be taken while applying 0, 5, and 10 Newtons (N) (± 0.25) of force onto the transducer and a measurement of the thickness of each single tissue layer will be taken in millimetres [22].

#### Flexibility tests of dorsal structures

Hamstring flexibility will be tested through the passive straight leg raise test. The participant will lie supine while the investigator passively raises the extended leg angular into hip flexion until a noticeable pelvic rotation and/or resistance is observed. Simultaneously, the investigator will palpate the ASIS of the ipsilateral pelvic side and fix an inclinometer (AcuAngle, Baseline) at the lateral malleolus level. Range of motion will be measured in degrees when a maximum position is reached [33, 34].

The flexibility of the lumbar spine will be measured using a double inclinometer method. With the participant standing, one inclinometer will be placed at the base of the sacrum and the other will be placed in the middle of the motion segments at the spinous processes of the thoracic vertebra (Th) 12 and L1 (Fig. 3). From a standing position, the participant will perform maximal spinal flexion, first eccentrically then concentrically, while keeping the legs extended. To do so, the participant will allow the upper body to bend down eccentrically with gravity. After that, she will be asked to engage muscles actively to reach a maximum range of motion. The difference between the sacral and the thoracolumbar inclinometers will determine lumbar flexibility in degrees [20, 35–37]. The flexibility test of the thoracic spine will follow the same protocol. The inclinometer at Th12 and L1 will be kept in position, while the second inclinometer will be placed onto the spinous processes of Th1 and Th2 [38–41].

#### Indentometry

Indentometry (IndentoPRO, Technische Universität Chemnitz) will be used to measure mechanical tissue deformation resistance at four different sites. Measurements will be taken within the treatment area 2.5 cm lateral to the interspinous space of the spinous processes L2 and L3. Further measurements will be taken 2.5 cm lateral to the spinous processes of Th6 and 20 cm distal to the ischial tuberosity on a connection line with the midpoint of the popliteal fossa. A reference point will be determined on the M. triceps brachii of the contralateral side 10 cm cranial to the olecranon on a connection line with the dorsolateral corner of the acromion (Fig. 3). The indentometry pin (1 cm^2^ surface area) will be put onto a measurement point with the circular reference plate (7.5 cm diameter) placed around it onto the surrounding tissue. Force will be applied at a constantly increasing rate of 5 N/s. At depths of 9 mm and 10 mm and at the pressure pain threshold (algometry), the applied force will be measured in N [23, 42–44]. In addition, during the pressure pain threshold, the indentation depth in mm will be registered. Pressure pain threshold is defined as an increasing sensation of pressure and a transition into feeling discomfort causing stinging, aching, drilling, or burning sensations that are clearly different from the feeling of pressure [44].

#### Superficial skin temperature

Superficial skin temperature will be measured in degrees Celsius at the same four sites as previously used for indentometry by using a multifunctional thermometer (FT70, Beurer Medical).

### Treatments

The treatment area stretches from the 12th rib down to the iliac crest and from the spinous processes to a line connecting the costal arch with the iliac crest.

#### IAMT group

IAMT will be performed using two different techniques and applying Fazer number two (Fig. 4) made by Artzt Vitality (Ludwig Artzt GmbH). The Fazer is made of medical stainless steel and is built to reach deeper structures better as well as treating broader tissue areas. It is a handy and ergonomic tool for the therapist to use, and it allows for more specialised and standardised treatment. The first technique will consist of short, shock-like frictions in the direction of movement. For the second technique, the Fazer will be slowly moved through the tissue creating a skin fold in front of it. Both techniques will be performed in only one direction. The convex side of the Fazer will be applied to reach, but not exceed, the pressure pain threshold. Skin contact will be maintained when returning the Fazer to the starting position. Both techniques will be applied in six different directions: first, from cranial to caudal longitudinally, then diagonally from medial to lateral, and finally from lateral to medial, followed by the same three directions from caudal to cranial. In every direction, the therapist will treat three overlapping lines. The lines will be completed one after another, from the medial to the lateral longitudinal line and starting from the diagonal line closest to the one furthest away from the therapist. After completing all three lines, a second round will be performed before the therapist continues with the next direction and the second technique (Fig. 5). To ensure quality standards, the intervention will be monitored by video. A lubricating film of pH-neutral cream will be applied to the treatment area to reduce frictional resistance and avoid skin redness.

**Fig. 4 Fig4:**
[figure not shown]
Fazer 2 by Artzt vitality (Ludwig Artzt GmbH)

**Fig. 5 Fig5:**
[figure not shown]
Schematic and chronological order of the instrument-assisted manual therapy techniques

#### Heat group

Heat will be applied through a hot pack with a surface area of 15 cm^2^ and an initial temperature of 55 °C (± 2.5) for a total of 8 min (treatment duration of the IAMT group).

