In healthy subjects, Griefahn et al. [24] found a significant increase in shear motion of the thoracolumbar fascia after a single treatment of the Mm. gluteus maximus, latissimus dorsi, and erector spinae with a foam roller in a placebo-controlled trial. Furthermore, the use of foam rollers and massage sticks has been shown to increase the maximum range of motion [25–27], improve vascular functionality [28], and reduce pain without compromising the development of strength, particularly in athletes [25, 26, 29]. In addition to these myofascial (self-)treatments, instrument-assisted manual therapy (IAMT) of the myofascial tissues is being increasingly implemented in usually prescribed regimes of 5 to 10 treatments. For this type of treatment, the therapist applies an appropriate amount of pressure on the myofascial tissue. Specific tools enable the therapist to reach the deeper layers of the tissue and target a more precise or extensive area. This kind of therapy is supposed to increase range of motion and functionality because of improved blood flow accompanied by increased tissue temperature, pain reduction as well as generated pressure, tensile, and shear forces. However, the underlying mechanisms behind these processes are still unknown, but increased microcirculation and altered expression of cytokines in the ground substance, particularly growth factors and inflammatory mediators that enhance regeneration and wound healing, are discussed [21, 30–32].

Through modern diagnostic ultrasound, novel and highly promising findings of both the structural and functional aspects of IAMT are anticipated to provide a greater understanding of its tissue effects.

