## Methods

### Study design

This randomised placebo-controlled pilot study will evaluate the feasibility of the planned measurements and generate the first information about the underlying effects of IAMT on structural and functional tissue properties of the lower back as recently reported in a pre-existing study on the lower leg [32]. Subjects will be recruited by a person who is not involved in the testing. The participants will be randomised into three even groups (1:1:1) using an adaptive biased-coin design (urn design), and they will receive an anonymised participant ID. The intervention group (IAMT group) will receive a standardised IAMT on the lumbar area. The comparison group (heat group) will receive heat therapy through an applied heat source, whereas the third group (placebo group) will undergo a pressure-less placebo treatment using an ultrasound transducer. All treatments will be performed once on the right side of the lower back by the same therapist. Testing, using a standardised protocol, will be conducted immediately before, immediately after, and 45 min after the treatment by a blinded investigator who is not involved in the treatments. The long-term evaluation will start with the first treatment, after which the IAMT group will receive nine further IAMT interventions twice a week over a five-week period, as usually practised in Germany, with a minimum of 48 h between treatments. The long-term effects of the IAMT will be controlled by the placebo group, which will be tested regularly over the 5-week period but not treated any more after the initial treatment and will act as a control group for the long-term effects of IAMT from this timepoint. Intermediate and final testing will be performed in weeks three and five, and a short questionnaire about subjectively perceived changes of flexibility and state of the lower back, as well as deviations in frequency and duration of the weekly training schedule, will be distributed before every intervention (Figs. 1 and 2).

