#### Placebo group

Placebo treatment will be performed without pressure over a duration of 8 min using an ultrasound transducer (Sono 5, Zimmer Elektromedizin) at 0.0 W/cm^2^. Using a conductive gel, the therapist will move the transducer (5 cm^2^) over the treatment area in a circular motion with moderate pace and without added pressure.

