## Discussion

To the best of the author’s knowledge, this proposed pilot study will be the first investigation to assess the feasibility and the quantitative impact of IAMT for the lower back on both structural and functional levels. The primary aims will be to evaluate the measurement methods used in terms of time economy and expressiveness and to create a basis to justify the sample size of future full studies.

The comparison of the ultrasound examinations with the previously more established indentometry and flexibility tests should provide information about the qualitative and quantitative properties of the novel ultrasound techniques especially in terms of their dependability and accuracy. Those results, in combination with the time economy and evaluation of the experts, are supposed to verify whether all the used measurements are necessary for future full studies.

To classify and quantify potential therapeutic effects of IAMT, possible confounding factors of the intervention, such as increased local blood flow and resulting tissue reactions or a therapist effect will be controlled by the heat group and by the attention and care the therapist gives to the placebo group. Modern and innovative techniques of ultrasound imaging initial and specific determination of thickness, compressibility, and shear motion of the single tissue layers might make it possible to examine the structural and functional properties of myofascial tissue after IAMT. These novel results may crucially provide a greater understanding of myofascial therapy, especially in IAMT of the lower back, and the potential impact of such therapy on myofascial chains. Moreover, the results may shed light on the mechanisms behind the effects of IAMT on the myofascial tissue and on the functional properties of the human body, for example, receptor stimulation or release of adhesion and fibrosis. This would allow for a better understanding of the benefits of IAMT and its subjectively perceived effects.

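### As written, the 15 cm² hot pack is smaller than any plausible treatment area, so unless the figure is a slip, heat matches IAMT in duration but not in treated area

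*Protocol article*

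**What the plan says.** **The treatment area.** The Treatments section opens with one definition, placed before the three arms are described. The area "stretches from the 12th rib down to the iliac crest and from the spinous processes to a line connecting the costal arch" and the iliac crest. No dimensions are given. Study design adds that every arm is treated on the right side only.

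**IAMT.** The tool "is built to reach deeper structures better as well as treating broader tissue areas" (IAMT group). The technique runs in six directions, and "In every direction, the therapist will treat three overlapping lines".

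**Placebo.** The transducer head is only 5 cm², but the therapist moves it "over the treatment area in a circular motion with moderate pace and without added pressure" (Placebo group).

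**Heat.** The Heat group section reads: "Heat will be applied through a hot pack with a surface area of 15" cm², at an initial 55 °C (± 2.5) for 8 min, with the 8 min tied to the length of the IAMT treatment. It gives no position, no movement and no second pack. Study design likewise says that this group "will receive heat therapy through an applied heat source".

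**Purpose of the heat arm.** The Discussion lists confounding factors "such as increased local blood flow and resulting tissue reactions or a therapist effect will be controlled by the heat group", together with the attention given to the placebo group. The Background says that IAMT is "supposed to increase range of motion and functionality because of improved blood flow accompanied by increased tissue temperature", among other reasons.

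**The concern.** The heat arm has a specific task in the short-term comparison: to separate a mechanical effect of IAMT from what increased blood flow and warming would produce anyway. It can do so only for tissue that it warms. Two arms are described as covering the defined treatment area, whereas the heat arm is given one small pack with no described movement.

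The outcome most exposed is lumbar flexibility. According to Flexibility tests of dorsal structures, it is measured between the sacral base and Th12/L1, so it reflects the whole lumbar segment and not one spot. Abstract and Aims make flexibility secondary, but Statistical analysis names it beside shear motion among the main outcomes to be modelled over the three short-term time points. The Background itself links blood flow and tissue temperature to range of motion.

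If heat reaches only part of the area that IAMT works on, a larger short-term gain in lumbar flexibility after IAMT could reflect wider warming or blood flow. That is the explanation the heat arm was meant to address, and a group-by-time model cannot recover it. If the figure is only a slip, the harm is different: this pilot is meant to inform full studies, and one that copied the text would use the wrong comparator.

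**Working it through.** There is no derived figure in the plan to reproduce. The check is geometry on a stated size.

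**Inputs from the protocol article**
- Hot pack: 15 cm² (Heat group).
- Treatment area: landmarks only (Treatments).
- A point 2.5 cm lateral to the midline at L2/L3 lies inside the treatment area (Indentometry).
- Ultrasound transducer length: 3.8 cm (Ultrasound scan), used only as a yardstick.

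**Step 1: size of the pack**
- As a square: side = √15 = 3.87 cm.
- As a circle: diameter = 2 × √(15/π) = 4.37 cm.
- The square pack is thus about as long as the ultrasound transducer.

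**Step 2: what the anatomy would have to be for the pack to suffice**

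Treat the area as a rectangle (an assumption). Full coverage then requires height × width ≤ 15 cm².
- The Indentometry section places a point 2.5 cm out inside the area, so the width there is at least 2.5 cm. At that minimum, the rib-to-crest height could be at most 15 / 2.5 = 6.0 cm.
- If the height were only the 3.8 cm transducer length, the lateral edge could lie at most 15 / 3.8 = 3.95 cm from the spinous processes.

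These are conditions for full coverage. They do not measure the area. The step from here to a shortfall rests on ordinary anatomy, since the lateral border runs from the costal arch to the iliac crest.

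**Step 3: coverage over an assumed range**

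Assumption, not in the protocol: one-sided height 6 to 12 cm and width 6 to 12 cm. Coverage = 15 / (height × width).

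| Assumed area | Coverage | Area ÷ pack |
|---|---|---|
| 6 × 6 = 36 cm² | 42% | 2.4 |
| 8 × 8 = 64 cm² | 23% | 4.3 |
| 10 × 10 = 100 cm² | 15% | 6.7 |
| 12 × 12 = 144 cm² | 10% | 9.6 |

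The pack is smaller than the area throughout the range. The degree varies fourfold (9.6 / 2.4 = 4).

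**Step 4: a yardstick that does not help**

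The 7.5 cm indentometry reference plate has area π × 3.75² = 44.2 cm², or 44.2 / 15 = 2.9 times the pack. It sets no lower bound on the treatment area. Centred 2.5 cm from the midline, it extends 3.75 − 2.5 = 1.25 cm past the midline and so outside the area. Only the measurement point is stated to lie inside.

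**Step 5: if the figure is a slip**

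A 15 cm × 15 cm pack would be 225 cm², which is 225 / 15 = 15 times the stated size and more than the largest assumed area of 144 cm². The protocol does not say that this was meant.

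**The case against.** **The plan promises matching on duration only.** This is true. The Heat group section ties the 8 min to IAMT and says nothing about area, and the Discussion does not mention equal area or lumbar flexibility. Full coverage would not by itself make warming or blood flow equal between a 55 °C pack and IAMT. What remains is that the Discussion relies on the heat group as a blood-flow control, and a pack over part of the area cannot support that for tissue it does not reach.

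**The treatment area has no stated size.** This also stands. A reader might infer from the numbers that the pack is far too small, or quote one coverage percentage. The protocol supports neither: the percentages rest on assumed dimensions, and only the direction is firm.

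**The consequence is narrow.** This is correct. A reader might infer that shear motion, the ultrasound primary outcome, is compromised. It is read midway between L2 and L3, and a pack placed there could warm that site. Skin temperature is measured at L2/L3 as well, so local surface warming can be compared between arms, although this does not show coverage of the wider area. Straight leg raise and thoracic flexion need not be affected either. The long-term comparison involves only IAMT and placebo.

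**The heading covers all three arms, and a condensed article may omit placement.** Heat over the same area is a natural reading of the Treatments section, and omitted placement would be no fault in itself. But the pack size is stated, and as stated it does not fit that reading.

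**The placebo head is smaller still.** This does not help, because the head is moved over the area and no movement is described for the pack.

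**Conclusion.** The point holds in a limited form, at minor to moderate severity. Taken literally, the heat arm uses one 15 cm² pack, about 3.9 × 3.9 cm, with no movement described. That is smaller than the treatment area across the assumed 36 to 144 cm². Either the figure is wrong, or heat matches IAMT in duration but not in treated area.

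In the second case, the Discussion's blood-flow control claim is not supported for outcomes spanning the whole lumbar region. In practice this means the short-term IAMT-versus-heat contrast on lumbar flexibility, a secondary outcome in a pilot. How large any distortion would be is unknown, because the protocol gives neither area dimensions nor thermal data. Outcomes read at L2/L3, the placebo contrast and the long-term results need not be affected.

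The conclusion rests on two assumptions: that the one-sided treatment area exceeds 15 cm² on ordinary anatomy, and that the absence of any described movement or second pack means that there is none.

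**What to change.** Correct the Heat group section to a pack size that covers the area defined under Treatments. If 15 cm² is truly the pack used, add one sentence stating that it is placed over the L2/L3 measurement site. Add another in the Discussion limiting the blood-flow control claim to outcomes read there (shear motion, thickness, compressibility and L2/L3 indentometry), which leaves out lumbar flexibility.

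The cost is one corrected figure or two added sentences. Sample size, visits and analysis do not change.

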#### Placebo group

Placebo treatment will be performed without pressure over a duration of 8 min using an ultrasound transducer (Sono 5, Zimmer Elektromedizin) at 0.0 W/cm^2^. Using a conductive gel, the therapist will move the transducer (5 cm^2^) over the treatment area in a circular motion with moderate pace and without added pressure.

### Statistical analysis

Statistical analysis will be performed with SPSS Statistics 25 (IBM). Usual descriptive statistics will be used to summarise the results. Means per group, mean differences between the groups will be outlined with standard deviation, 95% confidence interval, minimum, and maximum. Baseline sample characteristics of the groups will be compared by using a single factor analysis of variance or in case of missing assumptions with the Kruskal-Wallis test. Qualitative variables like experiences in myofascial self-treatments and “preferred free leg” will be analysed by using a chi-squared test. Main outcomes like shear motion (distance in mm) and flexibility (range of motion in degree) will be analysed for the three measurement time points in the short-term evaluation as well as for all measurement time points of the IAMT group and the control group in the long-term evaluation by using a longitudinal generalised linear mixed model. Those analyses will include groups, time (measurement time points), and group by time interaction as fixed effects, each participant as random effect, and a covariance structure that provided the best fit for the model to obtain estimates of slopes before and after the treatment and compared between groups like age, experiences in myofascial self-treatments, and “preferred free leg”. The Kruskal-Wallis test will be used to compare the experts ranking of suitability of the measuring instruments, whereas the time economy of the measurement instruments used will be analysed by using a single factor analysis of variance, if the necessary assumptions will be met. To evaluate the quantitative expressiveness of the ultrasound measurements with those of the flexibility tests and the indentometry, their relationship will be analysed by Pearson’s correlation coefficient, if the outcomes will be distributed normally, otherwise Spearman’s correlation coefficient will be applied. The significance level for all tests will be 5%.

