## Aims

Therefore, this pilot study aims to investigate the feasibility and the impact of IAMT for the lumbar area on the structural and functional properties of the myofascial tissue of the lower back and adjacent motion segments in healthy female soccer players as a reference for sample size calculation of further full studies.

The primary outcomes will be a critical analysis of the time economy and expressiveness of the used measurement methods in terms of quality and quantifiability as well as the effect of IAMT on shear motion of the lumbar structures (subcutaneous tissue, fascia, and musculus (M.) erector spinae) obtained through ultrasound imaging and compared with heat application (short-term) and placebo treatment (short-term and long-term). Secondary outcomes will include thickness and compressibility of the lumbar structures as well as flexibility of the dorsal structures, mechanical tissue deformation resistance (indentometry), and superficial skin temperature. Further secondary outcomes will be the subjectively perceived flexibility and state of the lower back.

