### Measurements

First, anthropometric data including height and weight will be obtained, and information about the athletic career, individual lifestyle, training sessions, and subjectively perceived flexibility and state of the lower back will be collected through a questionnaire to identify differences between the three groups. Skinfold thickness of the lower back will be measured using a skinfold calliper. After a 2-min rest, both sides of the body will be tested using the following order of measurements: superficial skin temperature, mechanical tissue deformation resistance (indentometry), shear motion, thickness, and compressibility of the single tissue layers, as well as flexibility of the dorsal structures. Every athlete will then receive one of the three different types of treatment and undergo post-measurements. Testing will alternate between body sides, starting with the treatment side (Figs. 1, 2, and 3). All measurements will be taken three times in a row, except for ultrasound imaging and flexibility measurements. Mean values will be used for comparative analysis.

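### The mixed model for shear motion promises a pre-treatment slope that one pre-treatment test cannot give, and its valid group-by-time contrast forgoes the precision of baseline adjustment

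*Protocol article*

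**What the plan says.** The Aims section makes the critical analysis of the measurement methods primary, "as well as the effect of IAMT on shear motion of the lumbar structures". The Statistical analysis section names shear motion and flexibility as main outcomes and assigns both to a longitudinal generalised linear mixed model. It specifies: "Those analyses will include groups, time (measurement time points), and group by time interaction as fixed effects, each participant as random effect", with the covariance structure chosen by fit. The purpose of the model is given as "to obtain estimates of slopes before and after the treatment and compared between groups like age", and the list then continues with experience of myofascial self-treatment and preferred free leg. The pre-treatment test is one of the three short-term time points analysed as outcomes. No baseline covariate or common baseline mean is mentioned.

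The Study design section sets the schedule. Testing "will be conducted immediately before, immediately after, and 45 min after the treatment". For the IAMT and placebo groups, "The long-term evaluation will start with the first treatment", and "Intermediate and final testing will be performed in weeks three and five". The Measurements section adds: "All measurements will be taken three times in a row, except for ultrasound imaging and flexibility measurements".

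**The concern.** Three things in the model description do not fit together.

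- A slope before treatment needs at least two pre-treatment times, and the schedule has one.
- The sentence promises a comparison by three participant characteristics that do not appear among the model's fixed effects. A reader cannot tell whether they are covariates, subgroups or a slip for the treatment arms.
- The pre-treatment value is handled as one more outcome, so the randomised comparison does not use it as efficiently as it could.

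Shear motion is the primary effect outcome, and the pilot's effect information is meant to feed the sample size of later full studies. That use needs a named, estimable contrast and its variance. The stated target is not one, and the contrast the model can supply is not named.

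**Working it through.** **Inputs.** Test times come from Study design: one before treatment, two on the same day after it, then weeks 3 and 5. Fixed effects come from Statistical analysis. The minimum of 60 players (Participants) at 1:1:1 (Study design) gives 60/3 = 20 per arm. The protocol gives no standard deviation, effect size, power or pre/post correlation, so there is no figure of its own to reproduce. The correlation rho below is an assumption, shown as a range.

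**Step 1: can a pre-treatment slope be estimated?** Write the mean in each group with four columns: intercept, pre-treatment slope, change in level at treatment, post-treatment slope. With one pre-treatment time, set at −1, the slope-before column is −1 at that test and 0 elsewhere. The level-change column minus the intercept column gives exactly the same values, so the two cannot be separated.

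- Three short-term tests: rank 3 for 4 columns per group, and 9 of 12 over three groups.
- Weeks 3 and 5 added: still rank 3 of 4.
- A second pre-treatment time: full rank, 4 of 4 per group and 12 of 12 over three groups.

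Replicates would not help, because repeats at one time give no slope, and ultrasound is excluded from triplicate measurement anyway.

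**Step 2: the three characteristics.** The listed fixed effects are group, time and their interaction. A comparison by age, self-treatment experience or preferred free leg needs a term for that variable and, if slopes or changes are compared, its interaction with time. Neither is listed.

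**Step 3: is the estimable contrast sound?** With a free mean for each group at each time, the group-by-time contrast at one post-treatment time is the between-group difference in change from baseline. In a simulation of two arms of 20 with a true effect of 0.5 SD (20,000 runs), its mean was 0.501 at rho = 0.5 and 0.500 at rho = 0.8. It is unbiased.

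**Step 4: precision.** Assume equal variances over time, a common correlation rho, outcome SD = 1 and n = 20 per arm.

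- Free baseline means: variance = 2 × 2(1 − rho)/n.
- Baseline-adjusted or common baseline mean: variance = 2 × (1 − rho²)/n.
- Ratio, adjusted to planned: (1 − rho²)/[2(1 − rho)] = (1 + rho)/2.

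At rho = 0.5 this gives 2 × 2 × 0.5/20 = 0.100 against 2 × 0.75/20 = 0.075. The standard errors are 0.316 and 0.274. A generalised least squares calculation with all three short-term times and three arms gave the same 0.100 and 0.075.

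| Assumed rho | SE as planned | SE adjusted | Variance ratio | SE smaller by | Players per arm at which the adjusted analysis matches 20 as planned |
|---|---|---|---|---|---|
| 0.3 | 0.374 | 0.302 | 0.65 | 19% | 13 |
| 0.5 | 0.316 | 0.274 | 0.75 | 13% | 15 |
| 0.7 | 0.245 | 0.226 | 0.85 | 8% | 17 |
| 0.8 | 0.200 | 0.190 | 0.90 | 5% | 18 |
| 0.9 | 0.141 | 0.138 | 0.95 | 2.5% | 19 |

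The last column is 20 × (1 + rho)/2. The formula ignores the small cost of estimating the baseline coefficient. In the simulation, with baseline as a covariate, the standard error fell from 0.316 to 0.277 at rho = 0.5 (12%) and from 0.201 to 0.194 at rho = 0.8 (4%), slightly less than the formula gives.

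**The case against.** The best defence is that the listed model can be fitted, and that the word slopes may be loose language for change from before to after. The simulation supports the first part. The second is possible, but the text does not say so, and it names no contrast that would take the place of the slopes.

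Keeping the pre-treatment value as a repeated outcome is also standard and valid. That stands: baseline adjustment is an efficiency gain, not the repair of an error. The gain depends on a correlation that the documents do not report. For tests immediately and 45 minutes after a single 8-minute session a high correlation is plausible, and at 0.8 to 0.9 little is gained.

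A condensed article may leave the covariate specification to a fuller plan. That excuses brevity. It does not excuse a stated purpose that conflicts with the stated schedule, or a promised comparison that the listed terms cannot make.

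Three stronger readings are tempting, and the documents do not support them.

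- A reader might infer that the treatment effect as a whole is mis-targeted. Only the slope wording is; the group-by-time contrast targets the effect without bias. If the group main effect averaged over all three times were read as the treatment effect, a true 0.50 SD would shrink to 0.50 × 2/3 = 0.33, but nothing in the plan says it will be read that way.
- A reader might infer a single long-term slope running across minutes and weeks. The section describes time as measurement time points, which reads most naturally as categorical. It states neither continuous time nor a five-visit slope, and the schedule figures are not available here.
- A reader might call the analysis imprecise outright. It is only less precise than the alternative, by an amount that depends on rho.

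**Conclusion.** The point holds as a moderate one. The stated purpose of the model conflicts with the schedule: with one pre-treatment test, no slope before treatment exists to be estimated. This rests on the text alone and needs no assumption. The promised comparison by three characteristics has no counterpart among the listed fixed effects.

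The contrast that can be estimated is valid, but its standard error could be about 19% smaller at rho = 0.3 and only about 2.5% smaller at rho = 0.9. That range assumes 20 per arm, equal variances and a common correlation. There is no bias in the estimable contrast, and the trial is a pilot, so the matter is not critical. It is still worth correcting, because the effect estimate and its variance are meant to inform later sample sizes.

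**What to change.** Rewrite the sentence in the Statistical analysis section that describes the mixed model:

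- Delete the reference to slopes, and state that time is categorical.
- Name the treatment effect as the between-group difference in shear motion at each post-treatment time: immediately and 45 minutes after treatment (IAMT against heat and against placebo), and weeks 3 and 5 (IAMT against the placebo group).
- Either adjust for the pre-treatment value, with only post-treatment values as outcomes, or keep all times as outcomes and constrain a common baseline mean across arms.
- Enter age, prior myofascial self-treatment and preferred free leg as covariates, or drop that comparison.
- Report the observed pre/post correlation with the estimates. Later sample-size calculations need it, and it will show how much the adjustment gained.

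The cost is a few lines of text. No further data, visits or participants are needed.
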